# CryptoDex: A randomised, double-blind, placebo-controlled phase III trial of adjunctive dexamethasone in HIV-infected adults with cryptococcal meningitis: study protocol for a randomised control trial

**DOI:** 10.1186/1745-6215-15-441

**Published:** 2014-11-12

## Abstract

**Background:**

Cryptococcal meningitis (CM) is a severe AIDS-defining illness with 90-day case mortality as high as 70% in sub-Saharan Africa, despite treatment. It is the leading cause of death in HIV patients in Asia and Africa.

No major advance has been made in the treatment of CM since the 1970s. The mainstays of induction therapy are amphotericin B and flucytosine, but these are often poorly available where the disease burden is highest. Adjunctive treatments, such as dexamethasone, have had dramatic effects on mortality in other neurologic infections, but are untested in CM. Given the high death rates in patients receiving current optimal treatment, and the lack of new agents on the horizon, adjuvant treatments, which offer the potential to reduce mortality in CM, should be tested.

The principal research question posed by this study is as follows: does adding dexamethasone to standard antifungal therapy for CM reduce mortality? Dexamethasone is a cheap, readily available, and practicable intervention.

**Method:**

A double-blind placebo-controlled trial with parallel arms in which patients are randomised to receive either dexamethasone or placebo, in addition to local standard of care. The study recruits patients in both Asia and Africa to ensure the relevance of its results to the populations in which the disease burden is highest. The 10-week mortality risk in the control group is expected to be between 30% and 50%, depending on location, and the target hazard ratio of 0.7 corresponds to absolute risk reductions in mortality from 30% to 22%, or from 50% to 38%. Assuming an overall 10-week mortality of at least 30% in our study population, recruitment of 824 patients will be sufficient to observe the expected number of deaths. Allowing for some loss to follow-up, the total sample size for this study is 880 patients. To generate robust evidence across both continents, we aim to recruit roughly similar numbers of patients from each continent. The primary end point is 10-week mortality. Ethical approval has been obtained from Oxford University’s Tropical Research Ethics Committee (OxTREC), and as locally mandated at each site.

**Trial registration:**

International Standard Randomised Controlled Trial Number: ISRCTN59144167 26-July-2012

## Background and rationale

### Background

Cryptococcal meningitis (CM) is estimated to cause 625,000 deaths every year, most occurring within 3 months of diagnosis [1]. It is the leading cause of death in HIV patients in Asia and Africa, affecting 3.2% of the HIV-infected population per year [1]. The incidence in these regions is the highest in the world; in Africa, more deaths are estimated to be due to CM than to tuberculosis [1]. The 90-day case-fatality rate is up to 55% in Asia and 70% in Africa [1].

Despite improvements in access to HIV care, the WHO estimates that HIV/AIDS will be the leading cause of disease in middle- and low-income countries by 2015, and models suggest that, even if 80% access to HIV treatment is achieved by 2012, there will be 6.5 million AIDS deaths p.a. by 2030 [2]. Thus, CM is likely to remain a significant health burden for the foreseeable future.

No major advance has occurred in the treatment of cryptococcal meningitis since the 1970s. The mainstays of induction therapy are drugs that are more than 50 years old (amphotericin B and flucytosine), although these are often poorly available where the disease burden is highest. Although amphotericin therapy is undoubtedly superior to fluconazole monotherapy, amphotericin combination therapy has only recently been shown to reduce mortality when compared with amphotericin monotherapy. Whereas effective antifungal therapy is the key, adjunctive treatments, which have been seen to have dramatic effects on mortality in other neurologic infections, are untested in cryptococcal meningitis. Given the high death rates in patients receiving current optimal treatment, and the paucity of new agents on the horizon, adjuvant treatments offer the greatest potential to reduce mortality in CM.

This study aims to reduce the death rate from CM. The principal research question is as follows: does adding dexamethasone to standard antifungal therapy for CM reduce mortality? In this double-blind placebo-controlled trial (DBRCT) patients will be randomised to receive either dexamethasone or placebo. Dexamethasone is a cheap, readily available, and practicable intervention.

This multicentre study recruits patients in both Asia and Africa to ensure the relevance of the study results in the populations in which the disease burden is highest.

### Treatment of CM

Successful treatment of CM depends on effective antifungal therapy and successful management of complications, notably increased intracranial pressure (see Appendix 3). Antifungal treatment schedules for cryptococcal meningitis are not globally uniform but are affected by drug availability, costs, and human resources. The Infectious Diseases Society of America convenes an international panel to draw up treatment guidelines, most recently published in 2010, and the WHO currently has guidelines in development that will be specifically aimed at management in resource-poor countries. These conform closely to the IDSA guidelines. Treatment generally consists of a period of induction therapy by using high-dose or combination antifungal therapy (usually for 2 weeks), followed by a period of consolidation therapy of 8 weeks with fluconazole. After this time, provided that the patient has responded to treatment, secondary prophylaxis using lower-dose fluconazole is given to prevent disease relapse. It is generally considered safe to stop secondary prophylaxis if ARV therapy has resulted in suppression of the plasma viral load and immune reconstitution with recovery of the CD4 cell count to >100 cells/μl has lasted for at least 6 months).

Consistent with the local practices and the WHO and IDSA guidelines, in this study, patients will receive antifungal therapy consisting of amphotericin B (1 mg/kg/day) combined with fluconazole, 800 mg/day for 2 weeks, followed by fluconazole 800 mg/day for a further 8 weeks before switching to secondary prophylaxis [3, 4].

### Rationale for adjuvant treatment with dexamethasone

Several mechanisms exist through which dexamethasone may modify disease outcome in cryptococcal meningitis. Current IDSA guidelines suggest that corticosteroids may be beneficial in cryptococcal meningitis in patients who have cryptococcomas with mass effect, acute respiratory distress syndrome, or IRIS [4]. However, corticosteroids have never been tested in a randomised controlled trial. Of note, 150 of 381 patients in the ACTG trial of combination antifungal therapy in cryptococcal meningitis received steroids during the study. The Graybill (2000) *post hoc* analysis of these patients has some serious limitations (1997) [5, 6]. Steroids were prescribed at the discretion of the attending physician, and the reasons for prescription are unclear. The Graybill analysis was limited to just 41 of the 150 steroid recipients, and did not report their impact on mortality. Clinical success (defined as stabilisation or improvement at 2 weeks) was lower in the 41 steroid recipients analysed (66% versus 86%). Apparently worse mycologic outcomes in these 41 patients are impossible to interpret, because no adjustments were made for the antifungal therapy received, fungal load, or clinical severity at baseline, all of which are known to be important outcome predictors [7, 8]. The exclusion from the analysis of the vast majority of patients who received steroids means that it is impossible to draw robust conclusions about their effect and underlines the need for a trial.

In contrast with the article by Graybill, a study in HIV-uninfected patients with *C. gattii* meningitis found a 10-fold reduction in blindness in those who received steroids [9]. Moreover, in tuberculous meningitis (TBM), a disease that shares pathophysiologic features with CM, dexamethasone has been shown to improve outcome (RR of death, 0.69; 95% CI, 0.52 to 0.92; *P* =0.01) [10]. In this RCT, conducted in Vietnam, 545 patients were recruited, of whom 98 were HIV infected. In addition to the reduced risk of death, fewer adverse events were found in patients receiving dexamethasone [10].

### Potential mechanisms of action dexamethasone in CM

#### Antiinflammatory action

Cryptococcal meningitis is a chronic granulomatous meningitis, with foci of inflammation in the basilar meninges, cerebral mass lesions, and a lymphocytic cerebrospinal fluid (CSF). The basilar meningitis leads to impairment of resorption of CSF, and this, along with physical blockage of CSF drainage by yeast cells and conglomerations of capsule, is believed to contribute to the increased intracranial pressure seen in the disease [11]. The immune response in the mouse model mimics that seen in AIDS patients [12]. The effect of antiinflammatory agents has been tested in this model. Reduction of inflammation prolongs survival in mice infected with a lethal dose of *C. neoformans*[13]. Dexamethasone increases median survival from 19 to 26 days (*P* <0.05), a benefit preserved when dexamethasone is combined with amphotericin B [14]. Dexamethasone does not interfere with the pharmacologic properties of amphotericin or fluconazole [14, 15]. Moderation of the inflammatory response is postulated to be through microglial cells, a key in the immune response to CM [16].

#### Reduction of cerebral oedema and brain swelling

Cerebral oedema is a key feature of CM, and cryptococcal capsule has been shown directly to induce cerebral oedema [17]. Vascular endothelial growth factor (VEGF) is a potent inducer of vascular permeability and angiogenesis, which has been implicated in the pathogenesis of brain oedema [18, 19]. Elevated levels are seen in both the CSF and blood of HIV patients with cryptococcal meningitis, and cryptococcal capsule has been shown to induce VEGF production by monocytes, neutrophils, and peripheral blood mononuclear cells in a dose-dependent manner [18, 20]. *In vitro*, this induction is significantly downregulated by dexamethasone [18]. Downregulation occurs at a range of concentrations consistent with those achieved in human dosing. A rat model of brain oedema suggests that the effect of steroids on oedema is mediated through the inhibition of VEGF [21]. Corticosteroids reduce vascular permeability and limit oedema, and inhibition of VEGF may explain the beneficial effect of steroid therapy in TBM [10, 22].

#### Reduction of intracranial pressure

Increased intracranial pressure (ICP) is frequent in CM and is an important cause of mortality [5]. Dexamethasone reduces increased ICP in models of other brain infections [23–25]. The mechanisms are not clear, but through attenuation of inflammation, cerebral oedema, and restoration of the blood/brain barrier, it is plausible that dexamethasone may reduce increased ICP in CM.

#### Modification of cerebral vasculitis

Cerebral vasculitis, frequently described in infections, is a recognised feature of CM [26–29]. The pathophysiology of neurologic vasculitis is relatively well understood: the neurologic features arise principally through ischaemia and infarction secondary to inflammation [30]. In infections, the vascular insult may be mediated through any or all of vascular wall invasion, immune complexes, or cryoglobulins. Of these, both endothelial invasion and immune complex disease are described in cryptococcosis [31, 32].

Steroids are an important therapeutic option in primary cerebral vasculitides, and their beneficial effect in TBM may be through an antivasculitic action [30]. Attenuation of the vasculitis seen in CM may improve outcome.

### Potential harms of dexamethasone

Reported side effects of dexamethasone are well described and similar to those of other corticosteroids. Side effects include dysglycaemia, changes in mood, Cushing-like syndrome, gastrointestinal bleeding, immunosuppression, hypertension, and secondary hypoadrenalism. Side effects are more likely with higher doses (dexamethasone ≥16 mg/kg/day) and longer courses of treatment [33]. Dexamethasone is frequently prescribed for patients with intracranial pathology, including infectious diseases, and in addition, data on adverse events are available from large RCTs of dexamethasone that have been completed in tuberculous meningitis (TBM) and acute bacterial meningitis (BM) [10, 34–36]. In the BM trials, the duration of steroid therapy was 4 days, and in TBM, 6 to 8 weeks. In all these trials, adverse events, including potentially life-threatening adverse events such as gastrointestinal bleeding, were rare and were no more common in patients receiving dexamethasone compared with placebo.

In this study, patients will receive dexamethasone 0.3 mg/kg/day, reducing weekly over 6 weeks. This is the lower dose that was used in the TBM trial for patients with Grade I disease [10]. The risk and severity of any adverse events must be considered in the context of the high mortality seen in cryptococcal disease. Notably, dexamethasone has no mineralocorticoid effect and is not associated with hypokalaemia [37].

#### Immunosuppression

Corticosteroids are immunosuppressive. It is possible that they may slow yeast clearance from CSF, and increase the risk of other infections. However, animal studies suggest that dexamethasone improves yeast clearance from CSF [14]. Even if the rate of yeast clearance is reduced, this may not be detrimental. In this study, we will measure the rate of clearance of yeast from CSF (see Appendix 1). Patients with CM are profoundly immunosuppressed: the median CD4 count in Vietnamese patients is 16 cells/μl (which compares with a median CD4 count of 42 in Vietnamese HIV patients with tuberculous meningitis) [38]. Given this, whether dexamethasone will significantly increase the risk of other opportunistic infections (OIs) is not clear. The incidence of other OIs is a secondary end point of the study. Patients in the study will receive chemoprophylaxis against *Pneumocystis jirovecii* and other opportunistic infections, in line with national guidelines. Patients will be screened for TB at study entry as part of normal care.

#### Secondary hypoadrenalism

Adrenal suppression is a recognised risk in patients receiving corticosteroid therapy for prolonged periods or in higher doses. With a treatment course of the length in this study, adrenal suppression will be short lived and is prevented through the gradual reduction in dose, as stipulated in the protocol. Patients must be provided with an information card detailing the importance of taking the steroids as per the study protocol, and so that other doctors who attend them will be aware of their prescription. Steroid information cards must be provided in the local language. Steroids will be administered in a reducing dose according to best medical practice.

#### Hyperglycaemia

Reversible hyperglycaemia is a recognised side effect of corticosteroids. Hyperglycaemia is uncommon in patients receiving dexamethasone in this dose, with elevated fasting glucose occurring in fewer than 1% of patients and equally frequently amongst TBM patients receiving active drug or placebo [10]. A review of the adverse effects of corticosteroids in severe sepsis found an increased absolute risk of hyperglycaemia of 5.6% [39].

#### Cushing-like syndrome

A Cushing- type syndrome can develop in people receiving prolonged steroid therapy, with weight gain, redistribution of body fat, and acne. However, in the dose and duration given in this study, development of Cushing syndrome is unlikely. Moreover, it is reversible on treatment cessation.

#### Gastrointestinal bleeding

Data from TBM, bacterial meningitis, and sepsis suggest that corticosteroids do not increase the risk of gastrointestinal bleeding when used in these dosages and durations [10, 35, 36, 39].

#### Hypertension, salt retention, and hypokalaemia

These effects of corticosteroids are due to their mineralocorticoid action. Because dexamethasone belongs to the glucocorticoid group, the risk of these side effects is negligible.

### Overview of the trial

A multicentre double-blind randomised placebo-controlled trial of adjunctive treatment with dexamethasone in adults with HIV-associated cryptococcal meningitis

**Study aim:** To reduce mortality from cryptococcal meningitis in HIV-infected adult patients

**Intervention:** Dexamethasone in a reducing dose over the first 6 weeks of treatment

**Randomisation:** 1:1 study-intervention versus placebo, by using variably sized blocks and stratified by site

**Primary end point:** Survival during the first 10 weeks after randomisation

**Antifungal therapy:** Amphotericin B, 1 mg/kg/day + fluconazole 800 mg/day for 2 weeks, followed by fluconazole, 800 mg/day for 8 weeks, followed by secondary prophylaxis with fluconazole, 200 mg/day

**Secondary end points:** Survival during 6 months after randomisation, disability, rates of fungal clearance, rates of visual impairment, rates of IRIS, rates of new AIDS-defining illnesses, frequency of grade 3, grade 4, or serious adverse events, rates of increased intracranial pressure, time to new neurologic events, health economics analysis.

**Sample size:** 880 patients (roughly equal numbers from Asia and Africa)

**Participating countries:** Uganda, Malawi, Vietnam, Thailand, Indonesia, Laos

**Study sponsor:** Oxford University

**Study funding:** The UK Department for International Development, The Wellcome Trust (UK), and the Medical Research Council (UK) Joint Global Health Trials Scheme

**Study duration (recruitment and follow-up):** 3 years (Figures 1 and 2).

**Figure 1 Fig1:**
[figure not shown]
**Trial flow diagram.**

**Figure 2 Fig2:**
[figure not shown]
**Trial flow chart.**

## Study aims

### Primary aim

To investigate the effect of dexamethasone adjunctive therapy on 10-week survival in HIV-infected adult patients with cryptococcal meningitis

### Secondary aims

The secondary aims are to determine the effect of adjuvant treatment with dexamethasone on survival at 6 months, disability at 10 weeks and 6 months, the rate of sterilisation of cerebrospinal fluid (CSF), the frequency of grades 3, 4, and serious adverse events, the incidence of IRIS, the incidence of other opportunistic infections, repeated treatment for cryptococcal meningitis, the presence of visual deficit at 10 weeks, and health economics. In addition, the effect of steroids on survival by continent will be assessed.

## End points

### Primary end point

The primary outcome is overall survival until 10 weeks after randomisation.

### Secondary end points

#### Survival until 6 months after randomisation

Relapse occurs in cryptococcal meningitis. Most cases occur within 6 months of diagnosis. We will collect survival data at 6 months (alive versus date of death) to ensure that any survival benefit at 10 weeks is sustained at 6 months, and not negated by, for example, a higher relapse rate in patients receiving steroids.

#### Disability at 10 weeks and 6 months

Neurologic disability will be assessed by using the modified Rankin score and the Two Simple Questions and classified as good, intermediate, severe disability, or death, as previously described (Table 1) [10].

**Table 1 Tab1:** **Outcome and disability grading: “two simple questions” and rankin score**

The two simple questions		
Does the patient require help from anybody for everyday activities? *(For example eating, drinking, washing, brushing teeth, going to the toilet.)*	Yes/no	Yes = Poor outcome
Has the illness left you with any other problems?	Yes/no	Yes = Intermediate outcome
		No = Good outcome
**The modified rankin scale**		
**Grade**	**Description**	
0	No symptoms	
1	Minor symptoms not interfering with lifestyle	
2	Symptoms that lead to some restriction in lifestyle, but do not interfere with the patients’ ability to look after themselves	
3	Symptoms that restrict lifestyle and prevent totally independent living	
4	Symptoms that clearly prevent independent living, although the patient does not need constant care and attention	
5	Totally dependent, requiring constant help day and night	

Grade 0: Good outcome, Grade 1 or 2: Intermediate outcome, Grade 3-5: poor outcome.

Disability is an expected consequence of cryptococcal meningitis, including blindness, deafness, and other focal neurological deficits. In addition to reduced death rate, patients receiving dexamethasone may also have lesser (or higher) rates of these disabilities. The Rankin score and the Two Simple Questions are well-validated measures of the degree of disability in stroke survivors, and have been used frequently to measure disability after neurologic infections.

#### Rate of CSF sterilisation during the first 2 weeks

It is conceivable that dexamethasone could slow the rate of CSF sterilisation, although this is not seen in the animal model. In a subset of patients, we will measure the repeated fungal burdens in CSF over the first 2 weeks of treatment, model the rate of decline, and determine the effect of dexamethasone on fungal clearance. We will also determine whether the rate of CSF sterilisation is predictive of mortality in both study arms, based on joint modelling of longitudinal fungal counts and mortality. Specifically, the longitudinal model will be a mixed model with fixed effects for the intercept, time (that is, the slope), and a treatment-time interaction and random (bivariate normal) effects for the intercept and the slope. The Cox survival model will have shared random effects with the longitudinal model.

#### Adverse events

Comparison of the proportion of patients with any grade 3 or 4 adverse event and of serious adverse events between treatment groups will form an important part of the study analysis, to determine the safety of the intervention.

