#### Time to new neurologic event or death until 10 weeks

A neurologic event is defined as a decrease in Glasgow coma scale score by ≥2 points for ≥2 days from the highest previously recorded Glasgow coma scale score (including baseline) or the occurrence of any of the following adverse events: cerebellar symptoms, coma, hemiplegia, paraplegia, seizures, cerebral herniation, new-onset blindness or deafness, or cranial nerve palsy.

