## Definition and assessment of adverse events

### Definition of adverse events

An adverse event (AE) is any undesirable event that occurs to a study participant during the course of the study, regardless of whether that event is considered related to the study drug. An AE can, therefore, be any unfavourable and unintended sign (including an abnormal laboratory finding, for example), symptom, or disease temporally associated with the study drug, whether or not considered related to the study drug.

Examples include the following:

An increase in severity or frequency of a preexisting abnormality or disorder (events that are marked by a change from the participant’s baseline/entry status)All reactions from sensitivity or toxicity to study drugInjuries or accidents (for example, for a fall secondary to dizziness, “dizziness” is the event and the injury secondary to the fall is the “outcome”)New clinically significant abnormalities in clinical laboratory values, physiological testing, or physical examination.

Stable chronic conditions, such as arthritis, which are present before clinical trial entry and do not worsen are not considered AEs and will be documented in the subject’s clinical chart as medical history.

Clinical or laboratory events are considered adverse events only if they occur after the first dose of study treatment and before the patient completes trial participation. (See later for reporting of adverse events.)

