### Definition of serious adverse events

An AE is considered to be "serious" if it results in one of the following outcomes

Death,Life-threatening event (the subject was at immediate risk of death at the time of the event; it does not refer to an event that hypothetically might have caused death if it were more severe),Inpatient hospitalisation or prolongation of existing hospitalisationPersistent or significant disability/incapacity (a substantial disruption of a person's ability to conduct normal life functions),Congenital anomaly/birth defect,Important medical event that may not be immediately life-threatening or result in death or hospitalisation but may jeopardise the patient or may require intervention to prevent one of the other outcomes listed in the earlier definition.

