### Definition of unexpected serious adverse events

Unexpected serious adverse events are untoward medical events that fit one or more of the previously explained criteria for SAEs and that are not considered a part of normal clinical progression of disease or an expected drug reaction. Any event that becomes of concern to the investigators or study doctors during the course of the trial may be reported as a USAE.

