##### Adverse events

The frequency of serious and grade 3 and 4 adverse reactions as well as the frequency of specific adverse events will be summarised (both in terms of the total number of events as well as the number of patients with at least one event). The proportion of patients with at least one such event (overall and for each specific event separately) will be summarised and (informally) compared between the two treatment groups based on the Fisher Exact test.

**The rate of IRIS and the rate of relapse** (defined as antifungal treatment intensification or re-treatment) will be modelled with cause-specific proportional hazards models stratified by continent, taking into account the competing risk of prior death. Cumulative incidence functions for the competing events will also be calculated and displayed by treatment arm. Secondary time-to-event end points (time to new AIDS-defining illness or death and time to new neurologic event or death) will be analysed with Kaplan-Meier curves and Cox regression models, as described for the primary end point expressed earlier. The proportion of patients with blindness or visual deficit will be compared between the two arms with a logistic regression (as for the proportion of patients with good disability described earlier).

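### The pooled any-SAE proportion counts every death after the first dose, so in that one row a mortality benefit can cancel an excess of non-fatal serious harm (minor)

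*Protocol article*

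**What the plan says.** All references are to the protocol article.

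- **Purpose.** Under Secondary end points, Adverse events, safety is to be judged by "Comparison of the proportion of patients with any grade 3 or 4 adverse event and of serious adverse events between treatment groups". The frequency of serious adverse events is also named as a secondary end point in the trial overview and among the secondary aims.
- **What counts.** Definition of adverse events includes an event "regardless of whether that event is considered related to the study drug" and sets the start of counting: "Clinical or laboratory events are considered adverse events only if they occur after the first dose of study treatment". Counting ends when the patient completes participation.
- **What is serious.** Definition of serious adverse events opens its list of criteria with "Death,Life-threatening event (the subject was at immediate risk of death at the time of the event". Nothing there exempts deaths that are end-point events. The only allowance for disease progression is in the definition of unexpected SAEs, events "that are not considered a part of normal clinical progression of disease or an expected drug reaction". That category governs expedited reporting, not the comparison between arms.
- **How it is compared.** In Analysis of secondary end points, Adverse events: "The proportion of patients with at least one such event (overall and for each specific event separately) will be summarised". The sentence goes on to an informal comparison by Fisher's exact test.
- **Neurologic events.** The neurologic end point includes "the occurrence of any of the following adverse events: cerebellar symptoms, coma, hemiplegia, paraplegia, seizures" among its components, so these are adverse events as well as end-point events.

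**The concern.** Overall survival to 10 weeks is the primary end point, and these definitions make every death after the first dose a serious adverse event. The proportion of patients with any SAE is therefore the union of two things: dying, and having a serious event that was survived. If dexamethasone works as hoped, the first part falls. The pooled proportion can then stay level, or even favour dexamethasone, while the second part rises. If dexamethasone raises mortality, the deaths inflate the difference and the row largely repeats the primary result.

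This is a stated choice of summary, since the definition, the measure and the test are all given. It also differs from the treatment of IRIS and relapse in the same section, where death is handled as a competing event. What is at stake is how readily a reader can see, if mortality falls, the non-fatal price at which it fell.

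**Working it through.** **Inputs from the document:** target hazard ratio 0.7; control 10-week mortality 30% to 50%; 880 patients randomised 1:1, so 440 per arm; two-sided 5% level; Fisher's exact test for adverse events.

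**Assumed, because the document gives no figure:** the placebo proportion q with a non-fatal SAE (10% to 40%), and at first its independence from death.

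**Step 1. The plan's own figures reproduce.**
- Deaths needed: 4 × (1.960 + 0.842)² / (ln 0.7)² = 247, as stated. 247 / 0.30 = 823.3, so 824 patients, as stated.
- Mortality on dexamethasone: 1 − 0.70^0.7 = 22.1% and 1 − 0.50^0.7 = 38.4%, against the stated 22% and 38%.

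**Step 2. The pooled row.** With mortality m and non-fatal SAE probability q, P(any SAE) = m + (1 − m)q. For an illustrative 20% on placebo and 30% on dexamethasone:
- Lower mortality: 0.30 + 0.70 × 0.20 = 44.0% v 0.221 + 0.779 × 0.30 = 45.5%.
- Higher mortality: 0.50 + 0.50 × 0.20 = 60.0% v 0.384 + 0.616 × 0.30 = 56.9%. The row now favours dexamethasone.

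With 440 per arm, the chance that Fisher's test on the pooled row shows a significant excess on dexamethasone is about 6% in the first case and about 0.2% in the second. For non-fatal SAEs alone (20% v 30%) it is 91% to 92%.

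**Step 3. The excess that cancels exactly.** Setting the pooled proportions equal gives q on dexamethasone = 1 − (1 − pooled placebo proportion) / (1 − mortality on dexamethasone).

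| Placebo q | Cancelling q, deaths 30% v 22.1% | Excess (points) | Cancelling q, deaths 50% v 38.4% | Excess (points) |
|---|---|---|---|---|
| 10% | 19.1% | 9.1 | 26.9% | 16.9 |
| 20% | 28.1% | 8.1 | 35.0% | 15.0 |
| 30% | 37.1% | 7.1 | 43.1% | 13.1 |
| 40% | 46.1% | 6.1 | 51.3% | 11.3 |

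At each of these points the pooled row has about a 2% chance of showing a significant excess on dexamethasone. Example: for q = 20% at the lower mortality, 88 v 124 of 440 patients with a non-fatal SAE gives p = 0.006, while the pooled row is 194 v 194 and p = 1.0.

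**Step 4. Dropping independence.** Suppose the 20% v 30% applies to survivors, and a share s of those who die also had a non-fatal SAE. The proportion of all patients with a non-fatal SAE is then ms + (1 − m)q.

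| s | Deaths 30% v 22.1% | Power | Deaths 50% v 38.4% | Power |
|---|---|---|---|---|
| 50% | 29.0% v 34.4% | about 38% | 35.0% v 37.7% | about 12% |
| 80% | 38.0% v 41.0% | about 13% | 50.0% v 49.2% | about 1% |
| 100% | 44.0% v 45.5% | about 6% | 60.0% v 56.9% | about 0.2% |

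With strong overlap, a plain proportion with a non-fatal SAE inherits most of the masking.

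**The case against.** The strongest reply is that this is one row among several. The grade 3/4 comparison is named first in the same sentence as the SAE comparison. The generic grades stop at 4 and only grades 3 and 4 are recorded, so death is not itself counted there. Each specific event also gets its own test, so bleeding, hyperglycaemia or a particular infection would be visible. The comparison is labelled informal, so the power figures above describe a reading aid, not a decision rule. All of this stands. A reader might infer that the plan's safety analysis as a whole is blind to non-fatal harm; the document does not support that.

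Nor does it support the inference that the DMEC would be misled. Its report shows mortality by arm as a separate item, so a fall in deaths would be in plain view beside the SAE summary.

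A reader might also extend the masking to the neurologic end-point events. Those events enter the SAE row only if they meet a seriousness criterion, and masking through them needs a neurologic benefit as well as a survival benefit. The protocol itself allows for lower or higher disability rates, and nothing here quantifies that route. Likewise, the figures are for 10 weeks; larger masking over the 6 months of participation is not shown.

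Two further points partly stand. A fatal/non-fatal breakdown is a table detail that a condensed article may leave to the analysis plan. Its absence is therefore not the finding; the finding is the pooled comparison that the article does state. And separating deaths helps less when those who die usually have an earlier non-fatal SAE (step 4). That is plausible here, because life-threatening events and prolonged admission are seriousness criteria and all patients are inpatients for 14 days.

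**Conclusion.** The point holds for the pooled any-SAE proportion and no further. That row combines the primary end point with non-fatal serious harm. At the design hazard ratio of 0.7, a non-fatal excess of about 6 to 9 points (30% v 22% deaths) or 11 to 17 points (50% v 38%) would cancel in it. These sizes rest on assumed placebo rates of 10% to 40%, on independence from death, and on the planned mortality benefit being real. The comparison is informal, other safety comparisons remain, and no figure stated in the document is wrong. Severity is minor.

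**What to change.** Keep the all-SAE table. In Analysis of secondary end points, Adverse events, add a between-arm comparison of time to the first SAE whose outcome is not death. Use a cause-specific proportional hazards model stratified by continent, with death as a competing event and cumulative incidence shown by arm. This is the method the same section already sets out for IRIS and relapse.

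Define the event by its outcome, not merely by a seriousness criterion other than death. A fatal event will often also be life-threatening or prolong admission, and would otherwise re-enter the count. Show fatal and non-fatal SAEs separately in the final and DMEC tables. A sensitivity version that leaves out the neurologic end-point events, relapse and IRIS is optional.

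The cost is a little extra analysis and a few table rows, with no added patients or visits. It needs the onset date and outcome of each SAE. The article promises the date and cause of each death and sets SAE reporting times from occurrence, but does not list an SAE outcome field, so check that the case report form has one. The change does not remove the limit in step 4: non-fatal SAEs that precede death still count, and the cumulative incidence curves for SAEs and death should be read together.
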